### Central sensitization in patients with osteoarthritis of the knee

Central sensitization is defined as "an augmentation of responsiveness of central pain-signaling neurons to input from low-threshold mechanoreceptors" [14]. Central sensitization embodies modified sensory processing in the brain and malfunctioning of descending pain-inhibitory mechanisms [15]. The importance of central sensitization as a potential underlying mechanism of pain in OAk has recently gained interest [16]. In the past decade suggestions were already made concerning the influence of sensitization of wide dynamic range (WDR) dorsal horn neurons when explaining an increase of the mechanical pain threshold after applying a blockage of A -beta nerve fibers [17]. Continuous and intense nociceptive input from the OA-damaged knee joint may encourage central sensitization [18,19] and is assumed to play an important role in OA [20]. Central sensitization in patients with OAk was detected by Arendt-Nielsen and colleagues [16] by enhanced temporal summation (TS) of pain and impaired diffuse noxious inhibitory control (DNIC). TS is defined as an increase in pain rating after repetitive stimulation at a constant stimulus intensity [21]. It is thought to be a psychophysiological correlate of wind-up, which is defined as the increase in response magnitude of second-order nociceptive neurons and higher structures [22] to repetitive noxious stimulation [23]. DNIC is a phenomenon in which pain from one part of the body inhibits pain elsewhere in the body [21]. It appears that multireceptive WDR neurons in the dorsal horn of the spinal cord and trigeminal nociceptive play a key role in DNIC inhibitory processes [24]. These neurons are important convergence sites for both excitatory and inhibitory influences arising from more than one type of tissue and can be activated by both innocuous and noxious stimuli [25]. It has been suggested that DNIC functions as a filter, which allows the system to focus on a painful stimulus in a background of basic somesthetic activity. The mechanism appears to involve the spinal cord as well as supraspinal regions [25].

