### Aim of the proposed study

This study has a double aim. First to explore the pain inhibitory effect of burst tens in OAk patients. Second, to assess whether central sensitization affects this pain inhibitory effect. A 6 week burst tens intervention period will be succeeded by a 12 week follow up period. As an international consensus definition for central sensitization is lacking [26], we aim to assess the central sensitization by measuring pressure pain thresholds (PPT) at the knee (local pain) and at the upper limb (spreading pain) [27] and temporal summation before and during a heterotopic noxious conditioning stimulation [16,21]. The test-retest reliability of TS and DNIC has been reported as acceptable [21].

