### In- and exclusion criteria

To be included, patients need to be over 50 years old. All should have osteoarthritis in at least one knee fulfilling the American College of Rheumatology classification criteria [28] and report peak knee pain of more than 3 on a Numeric Rating Score (0-10 scale) over the last 24 hours.

Patients are excluded if they have had a knee surgery or intra-articular corticosteroid or hyaluronic acid injection [29] within 6 months, current or past (within 4 weeks) oral corticosteroid use, a history of knee joint replacement or tibial osteotomy, in case of contraindications to burst tens (pacemakers, epilepsy, dermatological conditions, abnormal sensation in the knees, pregnancy) or if they are unable to apply tens independently [7].

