### Outcome assessment

#### Primary outcome variable

The change from baseline to final assessment of the study knee in the continuous variables *"overall average knee pain" (KPa) and "peak pain over the last 24 h" (KPp*) will be measured using a numeric rating scale [32].

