#### Secondary outcome variables

The change from baseline to final assessment of the study knee in *self-reported knee pain and difficulty with physical function *will be measured using the WOMAC Index [32].

The *global perceived effect *(GPE) compared to baseline will be measured on an ordinal scale (1 - much worse, 2 - slightly worse, 3 - no change, 4 - slightly better, 5 - much better) [35]. The GPE is an overall measurement of the perceived effect of the patient. It has been used in various studies to assess therapeutic effects [36-38].

The change from baseline to final assessment of *medication use *will be recorded as another pain variable.

*Pressure pain threshold, temporal summation (TS) and *Diffuse noxious inhibition control (DNIC) will be used as baseline variables.

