### Data reduction and Statistical analysis

An intention-to-treat analysis will be performed so that the integrity of the randomization is ensured. Normality will be checked via the Shapiro-Wilk test.

To ensure good balance of participant characteristics in each group at baseline, stratification is used [39]. Changes in differences between both treatment groups after the intervention period (at 6 w and 12 w) will be analyzed using repeated measures ANOVA for the following variables: KPp, KPa, WOMAC subscores for pain and function, GPE. If the modulus of the partial correlation of potential confounding factors age and sex with the primary outcome values equals minimum 0.3, these covariates of prognostic values will be added as covariates in the ANOVA model [40].

As a secondary analysis, a linear regression analysis will be used with the following dependent factors: BMI, TS and DNIC; and as independent factors: KPa, KPp, WOMAC subscales for pain and function.

Significance value for all tests will be set at p < 0.05. All analyses will be performed using SPSS 20 for Windows.

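### The sensitization regression lists no baseline pain or function score as a covariate and does not say which pain values it uses, so a pooled association of TS or DNIC with pain may be spurious, with a sign that depends on the scale

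*Protocol article*

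**What the plan says.** The second aim is stated in Aim of the proposed study: "Second, to assess whether central sensitization affects this pain inhibitory effect". The one analysis directed at it is in Data reduction and Statistical analysis: "a linear regression analysis will be used with the following dependent factors: BMI, TS and DNIC; and as independent factors: KPa, KPp, WOMAC subscales". The sentence gives no time point or scale for the pain and function scores. It names no baseline score as a covariate, and no treatment term.

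The only adjustment covariates in that section are age and sex, and only for the other model. If their partial correlation with the primary outcome reaches 0.3 in absolute value, "these covariates of prognostic values will be added as covariates in the ANOVA model".

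Other relevant places:

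- Primary outcome variable defines the pain outcome as "The change from baseline to final assessment of the study knee in the continuous variables" KPa and KPp.
- Secondary outcome variables gives PPT, TS and DNIC a baseline role: "Diffuse noxious inhibition control (DNIC) will be used as baseline variables". The Follow up section has them measured again at 6 and 12 weeks.
- In- and exclusion criteria selects on pain. Patients must "report peak knee pain of more than 3 on a Numeric Rating Score (0-10 scale) over the last 24 hours".
- The Background section on central sensitization says "Continuous and intense nociceptive input from the OA-damaged knee joint may encourage central sensitization". It also presents sensitization as a possible mechanism behind OA knee pain.

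**The concern.** Baseline pain predicts the pain outcome. Patients who start high tend to fall further, by regression to the mean, yet still finish higher. Entry on a pain threshold adds to the first tendency. If TS or DNIC also varies with baseline pain, a regression without the baseline score lets the marker carry part of that relation.

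The sign of the artefact depends on a choice the plan leaves open. With change scores, more sensitized patients would seem to improve more, which would mask the adverse response the protocol anticipates. With raw follow-up scores they would seem to do worse, which would look like support for it. The Discussion speaks of the prognostic value of TS and DNIC and of finding non-sensitized patients who are likely to benefit. A pooled slope could easily be taken as an answer to that.

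**Working it through.** **The plan's own figure.** From Sample size: difference 2.9, SD 4.7, power 0.80, type I error 0.05 (two-sided assumed).

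- n per arm = 2 × [4.7 × (1.960 + 0.842) / 2.9]² = 41.2, rounded up to 42.
- After 15% loss: 42 / 0.85 = 49.4, rounded up to 50.
- After 10% each for age and sex: 50 × 1.2 × 2 = 120.

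The stated 42, 50 and 120 reproduce and are not at issue. The check below uses 120 × 0.85 = 102 evaluable patients.

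**Set-up (assumptions).** B is baseline pain and F is follow-up pain, with equal SDs. corr(TS, B) = ρ and corr(B, F) = r. TS has no effect on F given B. The documents give neither ρ nor r, so both are varied.

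**Formulas.**

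- Raw follow-up: corr(TS, F) = ρr.
- Change: corr(TS, F − B) = ρ(r − 1) / √(2 − 2r) = −ρ√((1 − r)/2).
- The signs are opposite whenever ρ > 0 and 0 < r < 1.
- Chance of p < 0.05 for a correlation c, by Fisher's z: Φ(|atanh c| × √99 − 1.960), plus the negligible opposite tail.

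**Example.** With ρ = 0.3 and r = 0.5, the raw correlation is 0.3 × 0.5 = +0.15 and the change correlation is −0.3 × √0.25 = −0.15. Then atanh(0.15) × √99 = 0.151 × 9.95 = 1.50, and Φ(1.50 − 1.96) ≈ 0.32.

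**False-positive rate for TS, baseline omitted, N = 102.**

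| ρ | r | raw | change |
|---|---|---|---|
| 0.1 | 0.3 | 6% | 9% |
| 0.1 | 0.5 | 8% | 8% |
| 0.1 | 0.7 | 11% | 7% |
| 0.2 | 0.3 | 9% | 22% |
| 0.2 | 0.5 | 17% | 17% |
| 0.2 | 0.7 | 29% | 12% |
| 0.3 | 0.3 | 15% | 43% |
| 0.3 | 0.5 | 32% | 32% |
| 0.3 | 0.7 | 56% | 21% |
| 0.4 | 0.3 | 22% | 67% |
| 0.4 | 0.5 | 52% | 52% |
| 0.4 | 0.7 | 82% | 34% |

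At ρ = 0 the rate is 5%. Least-squares simulation over the same grid agrees to within about two percentage points (about 6–69% for change, 6–83% for raw).

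**With B in the model.** The simulated TS slope is about zero and the rejection rate about 5%. Raw and change scores then give the same TS coefficient, because subtracting B from the outcome only shifts the coefficient of B by one.

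**Arm-by-TS term (not in the printed model).** Simulated with r = 0.5, a TENS effect of 0.62 SD (2.9 / 4.7) and ρ of 0.3 or 0.5:

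- If the TENS effect does not depend on baseline pain, leaving B out does no harm: rejection 4.5–4.8%.
- If the TENS effect grows by an assumed 0.3 SD per SD of baseline pain, the term is biased by about −0.09 (ρ = 0.3) to −0.15 (ρ = 0.5), and rejection is about 7–13%. Over a wider set of assumed values it is about 7–17%.
- In that second case a baseline main effect alone does not cure the bias (7.6% and 12.7%). Adding arm-by-baseline does (4.7–5.0%).

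**The case against.** **Baseline pain may already be in the model.** KPa, KPp and WOMAC are in the regression without a time point, and all are measured at baseline. This is fair as far as it goes. But if they are baseline values, the regression relates baseline pain to sensitization and says nothing about response to treatment.

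**The check is not the printed model.** As printed, the markers are the dependent variables and the pain scores the regressors. For one marker and one score the test of association is the same in either direction, so the artefact remains. The remedy, however, does need pain as the outcome, and adding a baseline score alone would not supply the missing arm-by-marker test.

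**The Background is cautious.** A reader might infer that the protocol calls baseline pain a driver of sensitization, so that a false sensitization effect is to be expected. The text does not support that. It says only that nociceptive input may encourage sensitization, gives no correlation, and does not refer to the baseline pain score. Its statement that "DNIC is a phenomenon in which pain from one part of the body inhibits pain elsewhere in the body" is a definition and adds little. TS pulses are set at each patient's own threshold and the cuff is titrated to a fixed pain rating, which weakens the presumption of a correlation without removing it.

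**Randomization protects the effect-modification test.** A reader might also infer that any arm-by-TS term would be biased. That holds only if TENS relief depends on baseline pain. The large rates in the table belong to a prognostic slope pooled over arms.

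**Adjustment changes the question.** If sensitization causes pain, baseline pain is partly its consequence, and an unadjusted marker association is a legitimate descriptive quantity. This stands.

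**Condensed article, exploratory analysis.** A fuller covariate list may exist in a document not shown. What is printed is nevertheless a specific variable list, and its scale is undefined. The primary comparison is unaffected.

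**Conclusion.** The point holds in a conditional form. The secondary regression lists no baseline score as a covariate and leaves the scale of the pain and function scores open. If TS correlates with baseline pain, a pooled TS association with pain can be spurious, and its sign turns on whether change or raw scores are used.

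The size rests entirely on assumed correlations. At 0.3 and 0.5 the false-positive rate is about one in three on either scale. At a TS–baseline correlation of 0.1 it is 6–11%, close to nominal at the low end. The same reasoning applies to DNIC, but no rate was computed for it, and the sign would depend on how DNIC is scored.

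This does not show that the trial will report a false sensitization effect, nor that a properly fitted arm-by-marker test would be invalid. It does mean that a pooled association should not be read as evidence that sensitization alters the TENS effect.

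**What to change.** Rewrite the regression sentence so that the outcome is follow-up (or change in) KPa, KPp, WOMAC pain or WOMAC function at a stated time point, and the predictors are arm, baseline TS or DNIC, arm-by-TS or arm-by-DNIC, and the baseline value of the same score. Raw and change scores then give the same arm, marker and interaction coefficients. Add arm-by-baseline score as a sensitivity analysis. State that an unadjusted marker association, if reported, is descriptive only.

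The cost is a rewritten sentence rather than an added clause, because the covariate helps only once pain is the outcome and the arm-by-marker term is present. No new data are needed, since every score is already collected at baseline.

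The statistical price is a slightly wider interval for the marker terms where TS and baseline pain are correlated. The standard error grows by roughly 1/√(1 − ρ²), which is 1/√0.84 = 1.09 at ρ = 0.4. For the arm-by-marker term this applies mainly in the sensitivity analysis. It is partly offset by lower residual variance: relative to unadjusted change scores the ratio is (1 − r²) / (2 − 2r) = (1 + r)/2, or 65–85% for r from 0.3 to 0.7.

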## Discussion

This study has a double aim. First, to explore the pain inhibitory effect of tens in OAk patients. Second, to assess whether components of central sensitization like temporal summation and diffuse noxious inhibitory control, affect this pain inhibitory effect.

It is believed that tens influences pain through different pathways. One of these pathways is the gate-control theory [9]. The second goal of our study protocol, i.e. exploring the potential prognostic value of TS and DNIC on the pain inhibitory effect of tens, is based on this rationale. However, opioid pathways that involve peripheral, spinal and supraspinal mechanisms [41,42] are also proposed as an explanation for the pain modulation of tens and this pathway may be less vulnerable for an adverse effect of tens in central sensitized OAk patients.

As tens may influence pain through the electrical stimulation of low-threshold A-beta cutaneous fibers, the responsiveness of central pain-signaling neurons of OAk patients who are centrally sensitized is augmented to the input of these electrical stimuli. This would encompass an adverse therapy effect of tens on the pain perception in patients with OAk who are centrally sensitized. Therefore we think that it might be interesting to identify a subgroup of symptomatic OAk patients, i.e., non-sensitized patients, who are likely to benefit from burst tens.

The majority of studies that were published in the past and that focused on treatment effects of tens, embody currents that were administered by a therapist in a practice or hospital setting. As portable tens devices are marketed as small, inexpensive, easy-to-use home units [13], we choose to use a self-administered protocol. This approach may encompass a positive influence on the patient's participation to the treatment as well as to the cost effectiveness of the treatment, as the machines that are used in (professional) practices are far more expensive than these portable tens devices.

To assess whether dose-effects may influence the treatment outcome, we plan to record the daily duration of the electro stimulation that is applied.

One major concern when using self-administered medical care is treatment adherence. We think that a weekly phone call after the initial start of the study may improve treatment adherence as well as stimulate participants to consistently fill out the diary.

We have chosen a daily treatment duration of 40 minutes continuously. This is based on the findings of Cheing and colleagues [43]. They found that the cumulative analgesic effect manifested by a tens group that received 40 minutes of tens therapy was significantly greater than those seen in 2 other active tens groups (20 and 60 minutes application) in the follow-up session, i.e. 2 weeks after termination of the 2 week treatment. They conclude that 40 minutes is the optimal treatment duration of tens to be used for the relief of pain in patients with knee osteoarthritis.

The results of this study will not only provide insight into the effect of tens but they may contribute to future studies investigating the identification of patient subgroups that may benefit from tens.

## List of abbreviations used

BMI: Body Mass Index; DNIC: Diffuse Noxious Inhibitory Control; GPE: Global Perceived Effect; KPa: overall average knee pain intensity; KPp: peak knee pain intensity; NRS: Numeric Rating Scale; OA: Osteoarthritis; Oak: Osteoarthritis of the knee; PPT: Pressure Pain Threshold; Tens: Transcutaneous Electrical Nerve Stimulation; TS:Temporal Summation; Stens: sham Transcutaneous Electrical Nerve Stimulation; WOMAC: Western Ontario and McMaster Universities; OI: Osteoarthritis Index; WDR: Wide Dynamic Range.
